### Pilot study

Prior to conducting the study, we will conduct a pilot study in which we will only recruit people in the USA. The aims of the pilot study will be to: ensure that recruitment and data collection function as anticipated; obtain data to more accurately estimate the necessary sample size; and determine how best to analyze the data.

### Allocation

Allocation to one of the six presentations will be determined by block-randomization. We have created a sequence of 600 presentation assignments by generating 100 blocks of the 6 presentations using [http://www.randomization.com](http://www.randomization.com/) (Randomization plan created on 17 April 2002, 16:03:41. To reproduce this plan use the seed 11049). This sequence will be looped and repeated until an adequate sample size is achieved.

The order in which we elicit the relative importance of the consequences of starting statins, VAS’s versus LTRS’s) will also be allocated by block-randomization.

### Data collection

Participants will enter responses directly by responding to the questions on the HIPPO website. The data generated will be stored anonymously in a database. Only completed records will be used in the main analyses.

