## METHODS

### Study design

The study is a Web-based randomized trial in which participants will be randomized to one of six ways of presenting information about CVD risk reduction listed above. The relative importance of the consequences of starting statins will be elicited in two ways (VAS’s and LTRS’s) for all of the participants. The order in which this is done will be randomized.

A printout of the Webpages that will be used is attached [Available as a supporting PowerPoint file, Figure S3.1 Facimile HIPPO Webpages for protocol]. Upon logging into the study Website, participants will be given information about the study and asked to give informed consent to participate. They will be presented with a brief scenario in which they are asked to imagine that they have elevated cholesterol and are given the option of taking pills that lower cholesterol (statins). The relative importance of CVD risk reduction, taking pills and costs will be elicited using VAS’s and LTRS’s. They will then be presented with information about the effect of statins on the risk of heart disease, using one of the presentations listed above, the need to take a pill each day and the out-of-pocket costs; and asked whether they would decide to take the pills or not. Baseline risk will then be altered in the direction that shifts the expected utilities towards the opposite decision; i.e. the baseline risk will be increased for respondents who decide not to take the pills and decreased for those who decide to take the pills. Participants will then be asked what they would decide again. After this they will be asked questions about their decision and about themselves and, finally, they will be asked which of the six ways of presenting CVD risk reduction they would prefer.

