### Analysis

We have the following variables:

UCVD = utility of having heart disease; i.e. 1 – how difficult it would be to have cardiovascular (“heart”) disease on a scale from 0 to 1; 1 equals the most difficult

UPill = utility of having to take a pill each day; i.e 1 – how difficult it would be to have to take a pill each day on a scale from 0 to 1; 1 equals the most difficult

UCost = utility of not having to pay for pills; i.e. 1 – how difficult it would be to have to pay an additional amount of money each month for equivalent to the out-of-pocket cost of taking a statin on a scale from 0 to 1; 1 equals the most difficult

PP = probability of having heart disease with taking pills

PN = probability of having heart disease without taking pills

Using these variables we can calculate the expected utility (EU) for a decision to take pills:

EU(taking pills) = PPּUCVD + (1 - PP)ּ(1-UCVD) – (1-UPill) – (1-UCost)

Operationally this transforms to:

EU(taking pills) = PPּ(1-VAS_hrt) + (1 - PP)ּ(VAS_hrt) – (VAS_pill) – (VAS_cost)

or not to take pills:

EU(not taking pills) = PNּUCVD + (1 - PN) ּ (1-UCVD)

Operationally this transforms to:

EU(not taking pills )= PNּ(1-VAS_hrt) + (1 - PN)ּ(VAS_hrt)

and the difference between these (A):
A = EU(taking pills) – EU(not taking pills)

The difference in expected utilities can range from positive values (in favour of taking pills) to negative values (in favour of not taking pills).

If G is used to represent the presentation group to which a participant is randomised and D represents the decision to take pills or not, then the relationship between D and A can be modelled as follows:

(Eq 1)          logit(D) = 0 + 1A

To examine the relationship between the model of what participants might be expected to decide based on the expected utilities of the two options (Eq 1) with how the information was presented, Eq 1 will be fit for each group G. We will then compare the fit between different groups by comparing the R2 between the different groups.

Using a maximum-likelihood model will allow us to adjust for other factors (age, gender, profession) in a natural way. This allows us to test for differences in professional background (scientists or engineers vs GPs or other health professionals vs others), and differences across countries (Canada vs Germany vs Norway vs USA). To the extent that any of these factors are confounders, adjusting for these factors would improve the precision of our model.

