#### ETHICS

The interventions in this study, alternative ways of presenting information on risk reduction, and asking the participants to make a hypothetical decision, are non-invasive and harmless. The same information presented in this study is widely available and is presented in many different ways, including those used in this study.10

Participants are informed on the consent screen that they can leave the study at any time, and they are given the option of having any data that they might have entered deleted.

Confidentiality of data entered by participants is ensured by not collecting any information that would make it possible to identify the participants. If participants fill out a form to request a report of the study results or they choose to participate in the lottery for a $100 gift certificate, their email or postal addresses will not be stored in the same database as their responses to the study questions.

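### Restricting the main analyses to undefined completed records can discard participants who already supplied everything Eq 1 needs, and can bias the comparison of R2 if leaving depends on agreement between A and D and differs by arm

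*Protocol*

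**What the plan says.** The Data collection section of the protocol fixes the analysis set in one sentence: "Only completed records will be used in the main analyses". No definition of a completed record follows, there or elsewhere.

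The Study design section gives the order of the web pages:

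1. Values: "The relative importance of CVD risk reduction, taking pills and costs will be elicited using" VAS and LTRS.
2. The randomised presentation is shown, with the daily pill and the cost, and participants are then shown the choice "and asked whether they would decide to take the pills or not".
3. Baseline risk is altered. "Participants will then be asked what they would decide again".
4. Questions about the decision and about the participant follow.
5. Last, "finally, they will be asked which of the six ways of presenting CVD risk reduction they would prefer".

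The Analysis section builds A from the three ratings and the two heart-disease probabilities, and "then the relationship between D and A can be modelled as follows" (Eq 1). Eq 1 is fitted in each presentation group and R2 is compared between groups. Age, gender and profession enter only in adjusted versions.

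The Ethics section allows participants to leave at any time and, separately, says "they are given the option of having any data that they might have entered deleted".

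**The concern.** The analysis set is tied to reaching the end of the questionnaire, whereas the primary model needs only items collected earlier. Someone who rates the consequences, sees the presentation, decides, and then closes the browser at the personal questions or the preference item has both A and D on record. On the ordinary reading of completed, that person is left out of the main analyses.

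Two things are at stake. The first is information: usable records are lost in an open-web study where early exit is expressly allowed. The second is validity. Completion comes after the randomised presentation and may be influenced by it. The measure compared is the strength of association between A and D, and the Sample size section reads a stronger association as better understanding. If people whose choice conflicts with their own stated values leave more often under one format, the remaining records in that arm look more consistent, and a poorer format could appear better.

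**Working it through.** **1. What Eq 1 needs and when it is available.** A needs the three ratings (step 1) and the probabilities, which the scenario sets. D is a decision, first recorded at step 2. Nothing from steps 4 or 5 enters unadjusted Eq 1. The Analysis section does not say whether D is the first or the second decision, but both come before steps 4 and 5.

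**2. The plan's own sample sizes.** For two independent correlations on the Fisher z scale, n per group = 2 × ((z(1-α/2) + z(power))/q)² + 3.

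- q = 0.30, α = 0.05, power 0.70: 140.16 (stated 140)
- q = 0.30, α = 0.05, power 0.80: 177.42 (stated 177)
- q = 0.40, α = 0.05, power 0.80: 101.11 (stated 101)

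All 12 rows reproduce to the nearest integer with this formula, which has no term for non-completion.

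**3. Power if 100 per group are recruited and some are excluded.** The 100 is the pilot minimum given under Sample size. The documents give no drop-out rate, so 10% to 40% is assumed. Power = Φ(q × √((n-3)/2) - 1.96), two-sided α = 0.05. For example, with q = 0.40 and n = 80: 0.40 × √38.5 = 2.482, and Φ(0.522) = 0.70.

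| Assumed loss | Usable per group | Power, q = 0.40 | Power, q = 0.30 | Recruits needed for 100 usable |
|---|---|---|---|---|
| 0% | 100 | 0.80 | 0.55 | 100 |
| 10% | 90 | 0.75 | 0.51 | 112 |
| 20% | 80 | 0.70 | 0.46 | 125 |
| 30% | 70 | 0.64 | 0.41 | 143 |
| 40% | 60 | 0.57 | 0.36 | 167 |

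The last column is 100/(1 - loss), rounded up. It gives the cost if recruitment continues until 100 records are usable.

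**4. Bias in the compared measure.** Assumptions: A standard normal, D logistic in A with slope 0.5, 1 or 1.5, and R taken as the product-moment correlation of A with D. A decider is concordant when D matches the sign of A. The spurious q is atanh(R among completers) - atanh(R among all) in one arm, with no such selection in the comparison arm.

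| Leaving: concordant / discordant | Slope 0.5 | Slope 1 | Slope 1.5 |
|---|---|---|---|
| 20% / 20% | 0.00 | 0.00 | 0.00 |
| 15% / 30% | 0.07 | 0.07 | 0.06 |
| 10% / 40% | 0.15 | 0.14 | 0.12 |
| 10% / 50% | 0.22 | 0.20 | 0.18 |

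At slope 1, R among all is 0.41 and R among completers is 0.47, 0.52 and 0.56 in the three unequal scenarios. Overall loss across the unequal scenarios is about 18% to 26%.

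**5. Leaving that depends on the decision alone.** Suppose 70% choose the pills, and 10% of takers and 30% of refusers leave. The share of takers among completers is 0.7 × 0.9/(0.7 × 0.9 + 0.3 × 0.7) = 0.63/0.84 = 75%. Selection on D alone leaves the logistic slope unchanged and shifts only the intercept. With slopes 0.5, 1 and 1.5, R goes from 0.218 to 0.207, from 0.386 to 0.368 and from 0.499 to 0.477, so q changes by -0.01, -0.02 and -0.03.

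**The case against.** **The word is undefined.** Completed might mean only that the items a given analysis needs are present, and operational definitions of analysis sets are often left to a SAP, which is not shown here. This stands as a limit on certainty. It does not remove the point: the protocol states the rule, its ordinary reading is a record finished to the last page, and the same edit resolves either reading.

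**D is not tied to the first decision, and adjusted models need late items.** Both are true. Even if the second decision were meant, it precedes the questions that end the record. Adjusted models would have fewer records, but unadjusted Eq 1 would not.

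**Power may not fall at all.** The Allocation section says the sequence is repeated until the sample is adequate, and the final size is to be set after the pilot. If adequate counts usable records, drop-out costs recruitment instead. This stands. The power figures describe a pilot of 100 recruits per group, not the main trial.

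**A reader might infer that the rule breaks the randomised comparison.** The documents do not support that. They give no drop-out rate and no evidence that leaving differs by presentation. Equal leaving has no effect on R, and material bias needs leaving to depend on agreement between A and D and to differ between arms.

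**A reader might also point to the shift from 70% to 75% takers.** The arithmetic is right, but the share of takers is not what the primary analysis compares, and the same scenario barely moves q.

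**Conclusion.** The point holds as a defect in a stated rule. On the ordinary reading, the main analyses exclude randomised participants with complete data for unadjusted Eq 1, for reasons that arise after the presentation was seen.

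The bias is possible, not demonstrated. Under the assumed concordance-dependent rates in one arm only, the spurious q of about 0.06 to 0.22 ranges from below to about twice the 0.10 that the protocol calls small, but stays under the 0.30 and 0.40 used for planning. Decision-only leaving is negligible on this scale. The loss of precision is real only if the count of 100 per group refers to recruits; otherwise it becomes extra recruitment.

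Widening the set narrows the problem without removing it. Inclusion would still require a decision made after the presentation, and people who leave between the two cannot be recovered. Loss before the presentation is seen cannot be caused by its content.

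**What to change.** In the Data collection section, replace the completed-records rule with a defined main set: all randomised participants with the value ratings and the first decision recorded and no deletion request, analysed as randomised. In addition:

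- State in the Analysis section that D in Eq 1 is the first decision.
- Keep full completers as a sensitivity analysis.
- For outcomes asked later, use everyone who answered that item.
- Tabulate drop-out by arm and last page reached, so that loss before the decision is visible.
- Say whether the pilot target of 100 per group counts recruits or usable records.

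The cost is a few sentences, and the pilot is the natural place to settle it because one of its aims is to decide how to analyse the data. There are two small downsides. Models adjusted for age, gender or profession will have fewer records than unadjusted Eq 1. The site must also save entries page by page, which the deletion option in the Ethics section implies but does not state.

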### Analysis

We have the following variables:

UCVD = utility of having heart disease; i.e. 1 – how difficult it would be to have cardiovascular (“heart”) disease on a scale from 0 to 1; 1 equals the most difficult

UPill = utility of having to take a pill each day; i.e 1 – how difficult it would be to have to take a pill each day on a scale from 0 to 1; 1 equals the most difficult

UCost = utility of not having to pay for pills; i.e. 1 – how difficult it would be to have to pay an additional amount of money each month for equivalent to the out-of-pocket cost of taking a statin on a scale from 0 to 1; 1 equals the most difficult

PP = probability of having heart disease with taking pills

PN = probability of having heart disease without taking pills

Using these variables we can calculate the expected utility (EU) for a decision to take pills:

EU(taking pills) = PPּUCVD + (1 - PP)ּ(1-UCVD) – (1-UPill) – (1-UCost)

Operationally this transforms to:

EU(taking pills) = PPּ(1-VAS_hrt) + (1 - PP)ּ(VAS_hrt) – (VAS_pill) – (VAS_cost)

or not to take pills:

EU(not taking pills) = PNּUCVD + (1 - PN) ּ (1-UCVD)

Operationally this transforms to:

EU(not taking pills )= PNּ(1-VAS_hrt) + (1 - PN)ּ(VAS_hrt)

and the difference between these (A):
A = EU(taking pills) – EU(not taking pills)

The difference in expected utilities can range from positive values (in favour of taking pills) to negative values (in favour of not taking pills).

If G is used to represent the presentation group to which a participant is randomised and D represents the decision to take pills or not, then the relationship between D and A can be modelled as follows:

(Eq 1)          logit(D) = 0 + 1A

To examine the relationship between the model of what participants might be expected to decide based on the expected utilities of the two options (Eq 1) with how the information was presented, Eq 1 will be fit for each group G. We will then compare the fit between different groups by comparing the R2 between the different groups.

Using a maximum-likelihood model will allow us to adjust for other factors (age, gender, profession) in a natural way. This allows us to test for differences in professional background (scientists or engineers vs GPs or other health professionals vs others), and differences across countries (Canada vs Germany vs Norway vs USA). To the extent that any of these factors are confounders, adjusting for these factors would improve the precision of our model.

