Expected utility (or “expected value”) can be defined as follows: Under uncertainty where there is a p% chance of an outcome (X), say having angina or a heart attack, the expected utility is equal to pּUx + (1-p)ּUnot x where Ux represents the desirability (utility value) of the outcome and Unot x is the desirability of the alternative outcome (good health). If there is a p% chance of X and a q% chance of another outcome (Y), then the expected value is equal to [pּUx + (1-p)ּUnot x + qּUy + (1-q)ּUnot y]. Expected utility theory suggests that people making rational decisions should choose the option with the highest expected utility.4 The utility of outcomes, such as different health states, is usually expressed as being between zero and one (e.g. with death having a value of zero and a fully healthy life having a value of one, although some people consider some health states to be worse than death).

Expected utility theory has been questioned for a number of reasons, including problems with how utilities are measured and observations that people often do not, in fact, choose to maximize their utilities.5-9 Nonetheless, it can still be argued that as the expected utility for a decision, such as to take statins, increases one would expect that, on average, increasing proportions of people would choose to take the pills, if they are well informed. This argument does not depend on every individual choosing to maximize her utilities. Some people may make decisions based on other factors and it is difficult to accurately measure people’s utilities. Nonetheless, one would expect some degree of correlation between the expected utility of deciding to do something, such as taking pills, and the proportion of people who decide take the pills. The assumption underlying this study is that ways of presenting information about the effects of healthcare that result in decisions that are most consistent with individuals’ subjective expected utilities are best.

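### The expected-utility formulas value freedom from heart disease at 1 − UCVD instead of at one, so the benefit term in A has the wrong weight, and the wrong sign when VAS_hrt is below 0.5

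*Protocol*

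**What the plan says.** The Protocol's Background section sets out expected utility for one outcome. Probability p multiplies the utility of the outcome and 1 − p multiplies the utility of its alternative, where "Unot x is the desirability of the alternative outcome (good health" is the wording for the second utility. The same paragraph puts utilities on a scale "with death having a value of zero and a fully healthy life having a value of one".

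The Analysis section begins its definition of the heart-disease utility with "UCVD = utility of having heart disease; i.e. 1 – how difficult it would be to have cardiovascular", on a 0 to 1 scale where 1 is the most difficult. So UCVD = 1 − VAS_hrt. In the formula for taking pills, the no-disease branch is multiplied by 1 − UCVD, and the line ends in "1-UCVD) – (1-UPill) – (1-UCost". The operational line repeats this and ends in "VAS_hrt) – (VAS_pill) – (VAS_cost". The two lines for not taking pills use the same value for that branch.

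The quantity analysed is "A = EU(taking pills) – EU(not taking pills", closed by a bracket, and positive values are read as favouring pills. A is the only predictor in Eq 1, a logistic model fitted in each presentation group, and R² is compared between groups.

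Under Study design, baseline risk is changed after the first decision and is "altered in the direction that shifts the expected utilities towards the opposite decision": upwards for those who decline the pills, downwards for those who accept.

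**The concern.** The value of not getting heart disease should not depend on how bad heart disease is thought to be. Under the Background definition it is good health, fixed at one. Under the Analysis formulas it equals VAS_hrt, so a participant who is not much troubled by heart disease is also given a low value for being healthy.

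The Analysis section is also inconsistent within a single line. Pill and cost are charged as 1 − UPill and 1 − UCost, which are losses from a reference of one, while heart disease is set against 1 − UCVD.

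The substitution appears in both formulas and both operational lines, so it is not a slip in one place, and no section gives a reason for it. At stake is whether A is the expected-utility difference that the protocol itself defines. The presentations, and VAS against LTRS, are judged by how well A predicts decisions.

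**Working it through.** **Inputs.** Write V = VAS_hrt, K = VAS_pill, C = VAS_cost and d = PN − PP. The event-rate rows of Attachment 2 give the risks:
- normal risk, 6% to 4%: d = 0.02
- increased risk, 24% to 16%: d = 0.08
- decreased risk, 1% to 0.66%: d = 0.0034

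The protocol states no numerical value of A, so there is no figure to reproduce first.

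**A as written.**
EU(taking) = PP(1 − V) + (1 − PP)V − K − C
EU(not taking) = PN(1 − V) + (1 − PN)V
A = (PN − PP)V − (PN − PP)(1 − V) − K − C = d(2V − 1) − K − C

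**A under the Background definition (no-disease branch = 1).**
EU(taking) = PP(1 − V) + (1 − PP) − K − C
EU(not taking) = PN(1 − V) + (1 − PN)
A = dV − K − C

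**Benefit part of A (K = C = 0).**

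| Risk level | V | As written, d(2V − 1) | Background definition, dV |
|---|---|---|---|
| Normal | 0.2 | −0.012 | +0.004 |
| Normal | 0.3 | −0.008 | +0.006 |
| Normal | 0.5 | 0 | +0.010 |
| Normal | 0.8 | +0.012 | +0.016 |
| Normal | 1.0 | +0.020 | +0.020 |
| Increased | 0.3 | −0.032 | +0.024 |
| Increased | 0.5 | 0 | +0.040 |
| Increased | 0.8 | +0.048 | +0.064 |
| Decreased | 0.3 | −0.00136 | +0.00102 |

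The weight on risk reduction is negative below V = 0.5, zero at 0.5, too small between 0.5 and 1, and right only at 1.

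**Size of the error.** dV − d(2V − 1) = d(1 − V). Its maximum, at V = 0, is 0.02 at normal risk, 0.08 at increased risk and 0.0034 at decreased risk.

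**Second decision.** Going from normal to increased risk changes d by 0.08 − 0.02 = 0.06, so A as written moves by 0.06(2V − 1). At V = 0.3 that is −0.024, away from taking pills; under the Background definition it is 0.06 × 0.3 = +0.018. Going from normal to decreased risk changes d by 0.0034 − 0.02 = −0.0166. At V = 0.3, A as written moves by −0.0166 × (−0.4) = +0.00664, towards taking pills; under the definition it moves by −0.00498. Both shifts run against the stated purpose of the step.

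**What reaches Eq 1.** As written, A = 2dV − d − K − C. At one risk level, d is the same for everyone and the intercept absorbs −d. What is left is 2dV − K − C against dV − K − C, so V counts twice as much relative to pill and cost as it should. If risk levels are pooled, the constant is −0.02, −0.08 or −0.0034 depending on the level, and one intercept cannot absorb all three.

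**Illustration, under assumed distributions.** The protocol gives no distribution of marks. Take K and C uniform on 0 to 0.1, and V either uniform on 0 to 1 or Beta(4, 1.5).

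| Quantity | V uniform | V Beta(4, 1.5) |
|---|---|---|
| Share with V below 0.5 | about 50% | about 12% |
| Correlation of the two versions of A, normal risk | 0.991 | 0.996 |
| Correlation, increased risk | 0.945 | 0.963 |
| Sign of A differs, normal risk | 0.3% | 0.5% |
| Sign of A differs, increased risk | 5% | 8% |

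With K and C uniform on 0 to 1, the correlation exceeds 0.998 at both of these risk levels.

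**The case against.** A reader might infer that the primary analysis predicts the wrong decision for everyone with V below 0.5. The documents do not support that. The Analysis section does not classify decisions by the sign of A; it fits a logistic model with a free intercept and slope and compares R². At the first decision all participants face the same 6% to 4%, so the constant drops out and A still rises with V for everyone, including those below 0.5. The Background section adds that its argument does not need every individual to maximise utility. This part of the objection stands: at a single risk level the only error left in Eq 1 is the doubled weight on V.

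A reader might also infer that the second decision necessarily carries the sign error into the fit. The Analysis section does not say that the second decision enters Eq 1, and if each risk level were fitted separately the constant would again be absorbed. The sign matters if levels are pooled, or if the sign or shift of A is read directly, as the Analysis and Study design sections both do in words.

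Third, the numerical effect at normal risk is small in the illustrations, because pill and cost marks can reach a combined 2 while the benefit term cannot exceed 0.02 in absolute size. This stands as well.

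Finally, the analysis is provisional: the pilot is meant partly to settle how to analyse the data. That does not remove the point, because the alternatives in Attachment 1 that are spelled out also start from Eq 1 and hence from A.

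**Conclusion.** The formula is inconsistent with the protocol's own definition and should be corrected. This follows from algebra alone. The benefit term is d(2V − 1) where the definition gives dV, and the error of d(1 − V) reaches 0.02 at normal risk and 0.08 at increased risk. For V below 0.5, A contradicts the purpose of the baseline-risk step and the stated reading of its sign.

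The consequence for the primary comparison is narrower. In a fit at one risk level it is a doubled weight on V relative to pill and cost; in a pooled fit the constant also remains. The effect on R² depends on the distribution of marks, which is not given. It is probably small at normal risk, where pill and cost dominate A. Nothing in the documents shows that the error would change the ranking of the six presentations.

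**What to change.** In both expected-utility formulas of the Analysis section, replace 1 − UCVD by 1 in the no-disease branch. In both operational lines, replace VAS_hrt by 1 where it multiplies 1 − PP and 1 − PN. A then becomes (PN − PP)·VAS_hrt − VAS_pill − VAS_cost. Apply the same change to the LTRS version, and state whether second decisions enter Eq 1 and, if so, whether risk levels are pooled.

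The edit needs no new data and no change to the questions, but it is not free of side effects. At a fixed risk level it halves the weight of VAS_hrt in A, which makes A still more dominated by pill and cost. With V uniform on 0 to 1 and d = 0.02, the correlation of A with V falls from 0.27 to 0.14 if pill and cost marks are uniform on 0 to 0.1, and from 0.028 to 0.014 if they are uniform on 0 to 1 (all assumed distributions). The scaling of the pill and cost terms against the benefit term should therefore be reviewed in the same revision.
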